### Data management

On-site monitoring visits shall occur throughout the course of the clinical study by the chief investigator. The chief investigator shall permit and assist the sponsor (should they chose to monitor the study) to carry out verification of all study forms against data in the source documents, which shall occur as per the departmental policy for undertaking such activities. University College Hospital recognises that there is an obligation to archive study-related documents at the end of the study. The study master file will be archived at the University College London in accordance with the University College Hospital Standard Operating Procedure for Archiving of Investigator Site File (ISF) and Pharmacy Site File (PSF). It will be archived for a minimum of 5 years from the study end, and no longer than 30 years from the study end.

### End of protocol treatment

Reasons for going off study protocol include:
Completion of last follow-up visit 2 years after surgeryPatient non-compliance or withdrawal (the reason for discontinuation will be recorded in the case report form)Intercurrent death

All patients included into this study are free to withdraw from the study at any time without compromise to their future treatment. On withdrawal, patients will revert to the standard follow-up regimen for routine (non-study) THA at the study site. The end of study form will be completed and the reason for withdrawal documented. This form will also be completed if the patient is lost to follow-up or dies during the course of the study. Data to the point of discontinuation will be used for analysis.

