**Methods and analysis:**

This prospective randomised controlled trial will include 60 patients with symptomatic hip osteoarthritis undergoing primary THA. Following informed consent, patients will be randomised to CO THA (control group) or RO THA (investigation group) at a ratio of 1:1 using an online random number generator. Observers will review patients at regular intervals for 2 years after surgery to record predefined study outcomes relating to the accuracy of implant positioning, hip biomechanics, postoperative rehabilitation, clinical progress, functional outcomes, cost-effectiveness, and complications. Primary and secondary objectives will be used to quantify and draw inferences on differences in the efficacy of treatment between the two groups. Intention-to-treat and per-protocol population analysis will be undertaken. Intention to treat relates to the allocated treatment (CO THA or RO THA), and per-protocol refers to the actual treatment received by the patient. The following statistical methods will be employed to analyse the data: descriptive statistics, independent *t* test, paired *t* test, analysis of variance, Fisher exact test, chi-square test, and graphical displays. Ethical approval was obtained from the London-Bromley Research Ethics Committee, UK. The study is sponsored by University College London, UK.

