### Eligibility criteria

The inclusion criteria for this study are as follows: patient has symptomatic hip osteoarthritis requiring primary THA, patient fit for surgical intervention following review by surgeon and anaesthetist, patient aged between 18 and 80 years at time of surgery, patient able to give informed consent and agrees to comply with the postoperative review programme, and patient has sufficient mobility to attend follow-up clinics. The exclusion criteria for this study are as follows: patient undergoing revision surgery or second-stage THA, patients in whom the planned hip biomechanics are in a different position to the contralateral hip (e.g. developmental dysplasia of the hip or protrusio acetabuli), patient not suitable to have the planned study implants (e.g. requiring dual mobility component or cemented implants), patient had previous contralateral THA, patient is immobile or has another neurological condition affecting musculoskeletal function, patient already enrolled on another concurrent clinical trial, patient unable or unwilling to sign the informed consent form specific to this study, and patient unable to attend the study follow-up programme.

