All surgical procedures will be performed under the direct supervision of a single surgeon using the standard posterior approach. Trial implants will be used to assess hip stability, offset, soft tissue tension, and leg-length discrepancy prior to implantation of the permanent acetabular and femoral components in both treatment groups. Patients in both treatment groups will receive the standard or high-offset Accolade II femoral stem (Stryker Ltd., Mahwah, NJ, USA) and the trident acetabular shell (Stryker Ltd., Mahwah, NJ, USA). Patients in both treatment groups will undergo standardised inpatient and outpatient rehabilitation programmes. This will include six outpatient physiotherapy sessions at two-weekly time intervals. Patients will receive physiotherapy-supervised closed and open chain exercises to transition through four phases of rehabilitation with predefined milestones relating to the following: core strength and stability, lower limb proprioception, muscle strengthening, hip and knee range of motion, mobility with and without walking aids; ascending and descending stairs; and functional activities to return to pre-disease level of activity. Any deviations from the standardised proforma will be recorded and presented with the study findings.

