### Outcomes

All study patients will undergo review by two observers (one orthopaedic registrar and one clinical research fellow) at 6 weeks, 6 months, 1 year, and 2 years following surgery. During these follow-up times, predefined clinical, functional, and radiological outcomes will be recorded by these observers using case report forms (CRFs). The following outcomes will be recorded in all study patients:
Accuracy of achieving the planned implant positioning and hip biomechanics (horizontal centre of rotation, vertical centre of rotation, acetabular offset, femoral offset, and leg-length discrepancy) as assessed using CT scanograms performed postoperatively at 6 weeksOperating time (minutes)Time to hospital discharge (hours)Analgesia requirements during inpatient admission and postoperatively at 6 weeks, 6 months, 1 year, and 2 yearsPatient-reported outcome measures including Oxford hip score (OHS), Harris hip score (HSS), Hip disability and osteoarthritis outcome score (HOOS), University College Hospital hip (UCH) score, Western Ontario and Mcmaster Universities Osteoarthritis Index (WOMAC), and University of California at Los Angeles hip (UCLA) score preoperatively and postoperatively at 6 weeks, 6 months, 1 year, and 2 years following surgeryHealth-related quality of life as measured using European Quality of Life questionnaire with 5 dimensions for adults (EQ-5D) preoperatively and postoperatively at 6 weeks, 6 months, 1 year, and 2 yearsMobilisation distance (metres) and use of mobility aids during inpatient admission and postoperatively at 6 weeks, 6 months, 1 year, and 2 yearsRange of movement (degrees) in the hip joint in the supine position as assessed with a goniometer during inpatient admission and postoperatively at 6 weeks, 6 months, 1 year, and 2 yearsResource use and cost-effectiveness including comparisons between the two treatment groups relating to operating time, theatre efficiency, equipment and sterilisation costs, analgesia requirements, inpatient rehabilitation, time to discharge, outpatient follow-up, additional imaging costs, and need for further surgeryComplications

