### Statistical analysis

The analysis of the per-protocol population will be considered the primary analysis. The differences between the CO THA and RO THA groups will be analysed by calculating the difference from baseline, per patient, and a two-sided confidence interval for the difference between the changes from baseline values will be calculated. This confidence interval will cover the true difference in the percentage change from baseline with a probability of 95%. The following statistical methods will be employed to analyse the data: descriptive statistics, independent *t* test, paired *t* test, analysis of variance, Fisher exact test, chi-square test, and graphical displays. Assumptions of normality will be tested with the D’Agostino test. Assumptions of homogeneity of variance will be tested with Levene’s test. If the distributional assumptions are (severely) violated, non-parametric techniques, such as Mann-Whitney’s test will be employed. In the event that RO THA is converted to CO THA intraoperatively, analysis will be performed using the intention-to-treat population and the treatment actually received by the patients. Intraoperative conversion from RO THA to CO THA will be documented and presented and published as part of the study. All statistical analysis will be undertaken by a blinded observer. Statistical significance is set at a *p* value < 0.05 for all analyses, and all statistical analysis will be performed using SPSS software version 25 (SPSS Inc., Chicago, IL, USA).

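### Undefined non-compliance is grouped with withdrawal as a reason for going off study, so operated patients who still consent could be lost to later outcomes

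*Protocol article*

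**What the plan says.** The End of protocol treatment section of the protocol article gives three kinds of reason for going off study protocol: the last visit at 2 years, patient "non-compliance or withdrawal (the reason for discontinuation will be recorded in the case report form", and death. It then states: "On withdrawal, patients will revert to the standard follow-up regimen for routine (non-study) THA at the study site". The section closes with "Data to the point of discontinuation will be used for analysis".

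Four other places bear on this:

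- **Eligibility criteria.** An inclusion criterion reads "patient able to give informed consent and agrees to comply with the postoperative review programme". This is the only place that says what a patient is to comply with.
- **Surgical intervention.** On the rehabilitation programme: "Any deviations from the standardised proforma will be recorded and presented with the study findings". No removal from the study is mentioned.
- **Outcomes.** Patients are reviewed "at 6 weeks, 6 months, 1 year, and 2 years following surgery". The CT assessment of implant position and hip biomechanics takes place at 6 weeks; most other outcomes run to 2 years.
- **Abstract (Methods and analysis) and Statistical analysis.** Intention to treat follows the allocated operation, while "per-protocol refers to the actual treatment received by the patient". The plan also says: "The analysis of the per-protocol population will be considered the primary analysis".

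**The concern.** The intervention is a single operation. Once it is done, nothing the patient does later changes the treatment received, so poor compliance afterwards is no reason to stop measuring outcomes. Withdrawal of consent is different, because it removes the right to collect further data. The section puts the two in one item, describes the event as a discontinuation, and places it beside two events that necessarily end follow-up.

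If the item is applied as written, outcomes could be lost after randomisation from people who were still willing to provide them. Those people need not resemble the ones who stay. If the loss differs between arms, the later comparisons are no longer protected by randomisation, and the intention-to-treat analysis promised in the abstract would lack outcomes that could have been obtained.

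**Working it through.** **1. Does either analysis population need the rule?**

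- Intention to treat is defined by allocation, which is fixed before surgery.
- Per-protocol is defined by the operation received, which is fixed in theatre.
- Conduct after surgery enters neither definition, so discontinuing a non-compliant patient changes no one's membership of either population. It only removes outcomes from them.

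**2. Which outcomes are exposed?**

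| Outcome | Timing | Exposure |
|---|---|---|
| Centre of rotation on CT (primary) | 6 weeks | Only if the patient leaves before the scan |
| Functional scores, EQ-5D, mobility, range of movement, analgesia | 6 weeks to 2 years | Every visit after discontinuation |
| Outpatient and further-surgery parts of resource use | Through follow-up | The period after discontinuation |
| Serious adverse events | Trial-level period, to the last patient's 2-year visit | Reporting is not said to stop |

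**3. The plan's own sample size.** Inputs from the Sample size section: means 3.7 and 2.9 mm, SD 1.0 mm, two-sided 5%, power 80%.

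- Effect size: (3.7 − 2.9) / 1.0 = 0.8.
- The two-sample t test needs 25.5, rounded up to 26 per arm, so 52. This reproduces the stated figure.
- Attrition: 52 / 0.90 = 57.8, so 58. The stated 60 is within 2 patients, and the allowance is 60 − 52 = 8.
- Power at an effect size of 0.8 is 86.1% with 30 per arm, 82.2% with 27 (10% loss), 80.7% with 26 and 77.4% with 24 (20% loss).

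The allowance protects power for the primary endpoint. It does nothing against loss that is related to outcome.

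**4. Illustration of selective loss.** The document gives no rate of non-compliance and no difference in outcome, so both are assumed. Let a share f of one arm be taken off study, with outcomes on average d SD worse than those retained, whose mean is m.

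- Full-arm mean: (1 − f) × m + f × (m − d) = m − f × d.
- Shift in the observed arm mean: m − (m − f × d) = f × d.

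| f | d = 0.5 | d = 1.0 |
|---|---|---|
| 5% | 0.025 SD | 0.05 SD |
| 10% | 0.05 SD | 0.10 SD |
| 15% | 0.075 SD | 0.15 SD |
| 20% | 0.10 SD | 0.20 SD |

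With 30 in the arm, 20% is 30 × 0.20 = 6 patients. The between-arm difference shifts by the full f × d only if the other arm has no selective loss; equal selective loss in both arms would cancel. If the patients removed were doing better than the rest, the sign reverses.

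**The case against.** The strongest reply is that the passages can be read consistently. The only compliance named elsewhere is with the review programme. On that reading non-compliance means failing to attend study visits, the data are missing because the patient did not come, and rewording the item would not recover them. The closing sentence on data keeps partial data rather than discarding it. The article also condenses a fuller protocol, which may define the term.

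Much of this stands, and it rules out several stronger readings that a reader might infer:

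- *The plan orders data collection to stop for non-compliant patients.* This is implied, not stated. Return to routine follow-up is written only for withdrawal.
- *A patient who misses physiotherapy is removed, in contradiction with the Surgical intervention section.* No sentence says so. Rehabilitation deviations are simply recorded and presented.
- *Patients are removed for reasons related to recovery, on an unblinded judgement.* The document does not link non-compliance to recovery, and does not say who judges it.
- *The primary endpoint and safety data are compromised.* The CT is at 6 weeks and measures a position set at surgery. Six sessions at two-week intervals span at least 5 × 2 = 10 weeks, so rehabilitation attendance has little time to act before the scan. Serious adverse event reporting is defined for the whole trial period.
- *The bias is about 0.20 SD.* Removing exactly the worst-scoring 10% of one arm on a normal score does give 0.1755 / 0.90 = 0.195 SD, but this is an extreme one-arm case that nothing in the document supports.

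The reply does not dispose of the point. The same section names loss to follow-up separately, which suggests that non-compliance means something else. Even if it means missed visits, a patient who misses one could be taken off study although later visits, questionnaires or note review remain possible. The grouping with withdrawal is also a rule that the article states, not a detail it leaves out.

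**Conclusion.** The point holds in a limited form. The plan groups an undefined non-compliance with withdrawal as a reason for going off study. On the natural reading, an operated patient who still consents could be discontinued and contribute no later outcomes, with no benefit to either planned population. The exposure lies mainly in secondary outcomes from 6 months to 2 years.

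Neither the size nor the direction of any bias can be derived from the document. The range of about 0.03 to 0.20 SD rests on assumed values (5 to 20% of one arm removed, 0.5 to 1.0 SD difference, no offsetting loss in the other arm) and shows only the order of magnitude. This is an inexpensive improvement to a stated rule. It does not show that the trial's main comparison is unsound.

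**What to change.** Remove non-compliance from the reasons for going off study, or list it separately from withdrawal of consent and define it. Add one sentence to this effect: randomised patients who still consent remain in the scheduled 6-week CT and the 6-week to 2-year assessments, and in the intention-to-treat analysis, whatever their attendance. Record missed visits or rehabilitation sessions as deviations, in the way the Surgical intervention section already handles rehabilitation. Where a patient does not attend, use the medical-note review that the Consent section already covers.

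The cost is about one sentence, a matching line on the end of study form, and some extra effort chasing poor attenders. The change concerns data collection only; treatment and rehabilitation are unaffected.

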### Monitoring

The chief investigator will monitor the progress of the clinical study in the form of monthly research meetings for those involved in the trial. The chief investigator will be responsible for day-to-day monitoring and management of the study. The UCLH/UCL/Joint Research Office, on behalf of UCL as sponsor, will monitor and conduct random audits on a selection of studies in its clinical research portfolio. Monitoring and auditing will be conducted in accordance with the Department of Health Research Governance Framework for Health & Social Care (April 2005) and in accordance with the sponsor’s monitoring and audit policies and procedures. As per the protocol, the principal investigator will email the sponsor twice yearly with the following: delegation log, adverse event log, deviation log, and any annual progress reports sent to the Research Ethics Committee. Any adverse events will also be included in any publications or presentations relating to the trial.

### Peer review

The study protocol has undergone independent external peer reviewer. The suggestions and recommendations for improvement to the study design were implemented. The reviewers and sponsor re-examined the revised protocol documents and confirmed that all queries and suggestions had been fully addressed.

## Discussion

Accurate restoration of hip biomechanics and implant positioning in THA are important surgeon-controlled variables that affect clinical outcomes and implant survivorship [3, 5, 6, 12, 15, 18, 23]. CO THA is performed using preoperative radiographic templates and intraoperative anatomical landmarks to manually guide implant positioning. However, this hand-held conventional technique is associated with 38–47% of patients receiving acetabular components outside of the planned safe ranges [2, 3, 8, 10]. The development of RO THA has enabled surgeons to use preoperative CT scans to create patient-specific surgical plans for achieving optimal implant positioning and hip biomechanics, and an intraoperative robotic-arm to execute this plan with a high level of accuracy [6, 14, 15, 20, 25]. This prospective randomised controlled trial compares a comprehensive and robust range of clinical, functional, and radiological outcomes between CO THA versus RO THA. All operative procedures will be undertaken using a standard posterior approach, sitting and standing spinopelvic radiographs will be used to assess patient-specific functional pelvic kinematics, and identical implant designs will be used in both treatment groups. The findings of this study will enable an improved understanding of differences in CO THA versus RO THA with respect to patient satisfaction, functional outcomes, implant survivorship, cost-effectiveness, and complications.

## Trial status

Protocol: version 3.0; date 26 October 2018

Patient recruitment date: 1 December 2018

Estimated completion of the recruitment date: 1 December 2020

Estimated completion of the final follow-up: 1 December 2022

## Registration

Registry name: ClinicalTrials.gov; reference: NCT04095845. Date registered: 19 September 2019.

URL: https://clinicaltrials.gov/ct2/show/NCT04095845?cond=mako&draw=2&rank=7.

## Data Availability

The datasets used and/or analysed during the current study are available from the corresponding author on reasonable request.

## Abbreviations

CO THA: Conventional manual total hip arthroplasty
DSMB: Data Safety Monitoring Board
EQ-5D: European Quality of Life questionnaire with 5 dimensions for adults
HHS: Harris hip score
HOOS: Hip disability and osteoarthritis outcome score
OHS: Oxford hip score
RO THA: Robotic-arm assisted total hip arthroplasty
SAE: Serious adverse event
SF-12: Short form health survey of 12 items
UCLA: University of California at Los Angeles hip score
WOMAC: Western Ontario and McMaster Universities Arthritis Index
